## **7. Research interventions**

### **7.1 Research interventions**

#### **7.1.1 Description of Intervention**

Control group received treatment with HCQ (5mg/kg/day) and prednisone (0.5mg/kg/day); while MMF group received treatment with HCQ (5mg/kg/day) and prednisone (0.5mg/kg/day) plus MMF 500mg twice daily. Hydroxychloroquine is taken after meals and the manufacturer is Shanghai Pharmaceutical Co., Ltd, and the dosage form is tablets (100mg per tablet). The daily dose of mycophenolate mofetil is 500 mg twice daily, and the manufacturer is Hangzhou Zhongmei Huadong Pharmaceutical Co., Ltd., and the dosage form is capsule (250 mg per capsule).

Prednisone dose was tapered as follows: the initial dose was maintained for four weeks and then tapered 5mg every two weeks. When the dose reduced to 20 mg/day, it was tapered 5mg every month and then gradually to 0.1-0.2mg/kg/day. The taper of prednisone doses was determined by the physicians according to the assessment of the patients. Participants who met the criteria of severe flare were considered as having ended the trial and were treated with

increased doses of prednisone (more than 0.5mg/kg/day), immunosuppressive therapy or hospitalized for treatment according to the patients' condition and the physician's assessment.

### **7.1.2 Dosage and Administration**

Control group received treatment with HCQ (5mg/kg/day) and prednisone (0.5mg/kg/day); while MMF group received treatment with HCQ (5mg/kg/day) and prednisone (0.5mg/kg/day) plus MMF 500mg twice daily. Hydroxychloroquine is taken after meals, the manufacturer is Shanghai Pharmaceutical Co., Ltd., and the dosage form is tablets (100mg per tablet). The daily dose of mycophenolate mofetil is 500 mg twice daily, the manufacturer is Hangzhou Zhongmei Huadong Pharmaceutical Co., Ltd., and the dosage form is capsules (250 mg per capsule). Prednisone dose was tapered as follows: the initial dose was maintained for four weeks and then tapered 5mg every two weeks. When the dose reduced to 20 mg/day, it was tapered 5mg every month and then gradually to 0.1-0.2mg/kg/day. The taper of prednisone doses was determined by the physicians according to the assessment of the patients. Participants who met the criteria of severe flare were considered as having ended the trial and were treated with increased doses of prednisone (more than 0.5mg/kg/day), immunosuppressive therapy or hospitalized for treatment according to the patients' condition and the physician's assessment.

### **7.1.3 Establishment, preservation, and unblinding methods of trial drug codes and methods of unblinding in emergency situations**

Not applicable for this trial.

### **7.1.4 Items and times of clinical and laboratory examinations to be carried out**

Patients were observed for clinical manifestations, assessment of disease condition, detection of liver and kidney function, erythrocyte sedimentation rate (ESR), CRP, blood and urine routine, anti-dsDNA antibody levels, complement C3, C4, immunoglobulin, SLEDAI-2K score, SF-36 score, medication use, and adverse reaction (AEs) records.

Number of visits: at screening + 4 follow-up visits (week 24, 48, 72, 96).

## **7.2 Preparation/handling/storage/responsibility**

### **7.2.1 Responsibility**

The drugs involved in this study were purchased by the patients from the outpatient pharmacy, and each time the dosage was prescribed according to the doctor's prescription.

### **7.2.2 Composition, Appearance, Packaging and Labeling**

Prednisone: The manufacturer is Zhejiang Xianju Pharmaceutical, and the dosage form is tablet (5 mg per tablet);

Hydroxychloroquine: The manufacturer is Shanghai Pharmaceuticals, and the dosage form is tablet (100 mg per tablet).

Mycophenolate mofetil: The manufacturer is Hangzhou Zhongmei Huadong Pharmaceutical Co., Ltd., and the dosage form is capsule (250 mg per capsule).

### **7.2.3 Product Storage and Stability**

Stored at room temperature and protected from light.

### **7.2.4 Preparation**

The intervention drugs are fixed-package tablets and capsules, which require no additional preparation.

### 7.3 Measures to reduce bias: randomization and blinding

Participants were randomly assigned (1:1) using blocks of four to receive either MMF (MMF group) or a control treatment (Control group). A statistician from the Clinical Trial Center of Ruijin Hospital, [name], who was masked to trial allocation generated the randomization sequences by a computer algorithm. Then, random numbers were written on the cards and packed in sequentially numbered envelopes that were opened when the patients were enrolled in the trial. They were assigned to the trial group according to the number on the card. Eligible subjects were recruited from the Department of Rheumatology and Immunology of Ruijin hospital and Department of Rheumatology and Immunology of the other two clinical centers. [name] randomly assigned patients to different groups according to number sequence. Assessors were masked to the group allocation. Observers were masked to the group allocation and they were responsible for regular follow-up assessments. Data analysts ([name] and [name]) were not involved in patient assessment and treatment, and they were masked to the group allocation.

### 7.4 Follow-up and compliance

During the study, the patients were followed up for 4 times (week 24, week 48, week 72, week 96). Patients were observed for clinical manifestations, assessment of disease condition, detection of liver and kidney function, erythrocyte sedimentation rate (ESR), CRP, blood and urine routine, anti-dsDNA antibody levels, complement C3, C4, immunoglobulin, SLEDAI-2K score, SF-36 score, medication use, and adverse reaction (AEs) records at each follow-up visit time. Measures to strengthen the compliance of research subjects: regularly follow up reminders to the patients.

### 7.5 Research Intervention Commitment

Remind patients to follow up regularly and keep detailed records of each medication administered to patients, and check patients' medical records regularly.

### 7.6 Research plan

| Content \ Time               | Screening period | Follow-up period |         |         |         |
|------------------------------|------------------|------------------|---------|---------|---------|
|                              | Screening day    | Week 24          | Week 48 | Week 72 | Week 96 |
| Informed consent form        | √                |                  |         |         |         |
| Inclusion/Exclusion Criteria | √                |                  |         |         |         |
| Physical examination         | √                | √                | √       | √       | √       |
| SLEDAI-2000 Index            | √                | √                | √       | √       | √       |
| Blood routine examination    | √                | √                | √       | √       | √       |
| Urine routine examination    | √                | √                | √       | √       | √       |
| ALT&AST                      | √                | √                | √       | √       | √       |
| Scr                          | √                | √                | √       | √       | √       |
| ESR & CRP                    | √                | √                | √       | √       | √       |

|                     |   |   |   |   |   |
|---------------------|---|---|---|---|---|
| Complement 3 & 4    | ✓ | ✓ | ✓ | ✓ | ✓ |
| Anti-dsDNA antibody | ✓ | ✓ | ✓ | ✓ | ✓ |
| Immunoglobulin G    | ✓ | ✓ | ✓ | ✓ | ✓ |
| SF-36 score         | ✓ | ✓ | ✓ | ✓ | ✓ |
| Medication          | ✓ | ✓ | ✓ | ✓ | ✓ |
| Adverse events      | ✓ | ✓ | ✓ | ✓ | ✓ |

## 8. Study Intervention Discontinuation and Study Subject

### Discontinuation/Withdrawal

#### 8.1 Research Intervention Discontinuation

- 1) Patients who met the criteria of severe flare were considered as having ended the trial. Patients with severe flare were not eligible for the current treatment and need to be further evaluated by assessors, it may be necessary for them to discontinue study intervention, the patient will remain in the study to be evaluated for the remainder of the assessment visits.
- 2) Patients who met the criteria of severe flare were treated with increased doses of prednisone (more than 0.5mg/kg/day), immunosuppressive therapy or hospitalized for treatment according to the patients' condition and the physician's assessment.
- 3) Patients with mild-to-moderate flares continued to be followed up till the end of Week 96, and all flare episodes were recorded.
- 4) Patients with mild-to-moderate flares could increase the dose of prednisone (less than 0.5mg/kg/day) or nonsteroidal anti-inflammatory drugs.
- 5) For fever, rash, and arthritis, the dose of prednisone could be used at an initial dose of less than 0.5mg/kg/day, and following the assessment of symptoms, the dose could be increased to more than 0.5mg/kg/day if needed.
- 6) Any sign of kidney involvement (glomerular hematuria and/or cellular casts, proteinuria >0.5g/24hours (or spot urine protein-to-creatinine ratio (UPCR) >500mg/g), unexplained decrease in glomerular filtration rate (GFR)), renal biopsy was suggested to confirm the diagnose of LN.
- 7) The treatment of LN was provided according to the European Renal Association-European Dialysis and Transplant Association (ERA-EDTA) guideline.
- 8) The treatment of other organ involvement was provided following the 2019 European League Against Rheumatism (EULAR) recommendation.
- 9) Other situations:
  - a) Liver and kidney dysfunction (Alanine aminotransferase (ALT)/ aspartate aminotransferase (AST) > 2 times upper normal limits; creatinine clearance rate < 60ml/min),
  - b) Cancer,
  - c) Recent infection or hematologic diseases not caused by SLE,
  - d) Pregnancy or planned to be pregnant,
  - e) Patients not willing to join the study.

Other situations including liver or kidney dysfunction, cancer, recent infections or hematologic diseases not caused by SLE, pregnancy or planning to be pregnant, patient will also remain in the study to be evaluated for the remainder of the assessment visits.

## **8.2 Subject discontinuation/withdrawal**

Patients may withdraw from the study at any time at his/her own request. Patients could withdraw at the discretion of the investigator for safety, behavioral, or compliance reasons. The patient will be permanently discontinued from the study intervention and the study at that time. If the participant withdraws informed consent, future information will stop collecting, investigators may retain and continue to use any data collected before withdrawing of the consent.

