## **8.3 Lost to follow-up**

The follow-up period of this research is 96 weeks, and every 24 weeks is a follow-up interval. When the research subject stops the scheduled follow-up, fails to complete the prescribed procedures of the research, or the investigator cannot contact the research subject regarded as lost to follow-up. A participant will be considered lost to follow-up if he/she repeatedly fails to return for scheduled visits and is unable to be contacted by the study site.

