### **8.5 Primary outcome**

Flare proportion was defined as categorical variables, data were expressed in the form of frequency (percentages). The primary outcome was the proportion of patients with flares (including mild-to-moderate flares and severe flares) during follow-up. Safety of Estrogens in Lupus Erythematosus National Assessment-Systemic Lupus Erythematosus Disease Activity Index (SELENA-SLEDAI) Flare Index (SFI) was used for assessing disease flares in this trial. Pearson Chi-square or Fisher's exact tests were used to compare between-group differences. We first calculated the total flare rate, and then calculated mild-to-moderate flare rate and severe flare rate, respectively.

For the primary outcome, Bonferroni correction was used and two-sided at a significance level of 0.025. A more stringent statistical criterion was used. Relative risk (RR) was employed to compare the proportion of patients with the end point between MMF group and Control group. Severe flare-free survival proportion was estimated by using the Kaplan-Meier method in the intention to MMF group and Control group with a log rank test. Regarding patients who dropped out of the study, we collected all of the data during follow-up period. For patient who loss to follow-up, we did not collect the data for the subsequent time after lost to follow-up event. We used the ITT set for primary outcome calculation. All of the patients were included in the denominator. We estimated the severe flare-free survival proportion of the MMF group and Control group in both ITT and PP Set using the Kaplan-Meier method.

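### Protocol 8.1, 8.2 and 8.3 and SAP 8.5 disagree on when follow-up ends, so later flare data on reachable, consenting patients may be lost

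*Combined protocol and SAP*

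**What the plan says.** Four places govern when a patient stops being observed.

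- **Protocol 8.1** lists medical situations that bear on stopping the intervention: liver or kidney dysfunction, cancer, infection or non-lupus blood disease, and pregnancy or a plan for it. It says the "patient will also remain in the study to be evaluated for the remainder of the assessment visits". It makes similar provision for patients who stop the intervention after a severe flare. It does not mention behaviour or compliance.
- **Protocol 8.2** says: "Patients could withdraw at the discretion of the investigator for safety, behavioral, or compliance reasons". The next sentence is "The patient will be permanently discontinued from the study intervention and the study at that time". Consent has its own sentence: "If the participant withdraws informed consent, future information will stop collecting", with earlier data kept.
- **Protocol 8.3** defines loss to follow-up twice. Under its first definition it is enough that a subject stops the scheduled visits, "fails to complete the prescribed procedures of the research, or the investigator cannot contact the research subject regarded as lost to follow-up". No number of failures is given. Under its second, the patient "repeatedly fails to return for scheduled visits and is unable to be contacted by the study site", so both conditions must hold.
- **SAP 8.5** says: "Regarding patients who dropped out of the study, we collected all of the data during follow-up period". For patients lost to follow-up it says: "we did not collect the data for the subsequent time after lost to follow-up event". It uses the ITT set with every patient in the denominator and gives no rule for scoring a patient whose flare status is unknown.

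**The concern.** Stopping a drug and leaving a trial are different events. An intention-to-treat comparison of flares over 96 weeks needs the second to be rare. Section 8.2 joins the two for patients who have not withdrawn consent, and 8.1 separates them for an overlapping group. Nothing says which section governs. The first definition in 8.3 can also label a reachable patient as lost, and SAP 8.5 then closes data collection on that patient.

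At stake are the primary endpoint and the week-96 secondary endpoints (LLDAS, SF-36, SLEDAI-2000, prednisone dose) for those patients. Visits that were never made cannot be recovered at the analysis.

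Loss could also differ by arm. Protocol 6.5 masks only assessors, and 7.3 adds observers and data analysts. Treating physicians are not stated to be masked, and the Brief list shows no placebo. Only one arm takes MMF, for which protocol 2.4.1 names gastrointestinal and blood-count effects.

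**Working it through.** **Step 1: apply the rules to three patients.**

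- *Raised ALT/AST above the 8.1 limit, consenting and reachable.* Under 8.1 the remaining visits continue. Under 8.2, if the investigator withdraws the patient for safety, the patient leaves the study. The outcome depends on which section is applied.
- *Poor compliance, consenting and reachable.* 8.1 is silent. Under 8.2 the investigator may withdraw the patient, who then leaves the study. SAP 8.5 does not say whether this patient is a drop-out or a loss.
- *Misses week 48, returns at week 72 with a flare.* Under the first 8.3 definition the patient may already be lost, and SAP 8.5 records nothing further. Under the second the patient is not lost, and the flare is recorded.

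**Step 2: reproduce the plan's own figures.** Protocol 5.3 and SAP section 6 assume flare rates of 10% (MMF) and 30% (Control), 58 per group and 10% drop-out. Exact enumeration of the two-sided unpooled Z test gives power 0.8036 and actual alpha 0.0568 at a common 30% rate. Both match. 58 / 0.90 = 64.4, rounded up to 65, also matches. The sample size calculation itself is not affected by this point.

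**Step 3: how many patients could be involved.** 10% drop-out of 65 is 6.5 patients per arm. The assumed 10% MMF flare rate is also 0.10 x 65 = 6.5 patients. The planned losses are thus as numerous as the expected MMF events.

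**Step 4: illustrate the effect on the comparison.** Let d be the share of an arm removed, p the arm's flare rate (assumed the same in removed patients), and f the share of removed patients' flares that goes unseen. All 65 stay in the denominator and an unseen flare counts as none:

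observed rate = p x (1 - d x f)

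The shares d are assumptions, because the plan gives one overall drop-out figure. f is taken from 0.5 to 1. Type I error and power are exact, for the pooled Z test (equivalent to the Pearson chi-square) at 0.05.

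*No true effect, 30% in both arms:*

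| Removed, MMF / Control | Observed, f = 0.5 | Observed, f = 1 | Difference (points) | Type I error |
|---|---|---|---|---|
| none | 30.0% / 30.0% | 30.0% / 30.0% | 0 | 0.052 |
| 10% / 10% | 28.5% / 28.5% | 27.0% / 27.0% | 0 | 0.052 |
| 15% / 5% | 27.75% / 29.25% | 25.5% / 28.5% | -1.5 to -3.0 | 0.056 to 0.069 |
| 20% / 5% | 27.0% / 29.25% | 24.0% / 28.5% | -2.25 to -4.5 | 0.062 to 0.092 |

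For example, 0.30 x (1 - 0.15 x 0.5) = 0.2775 and 0.30 x (1 - 0.05 x 0.5) = 0.2925, a difference of -0.015. At the 0.025 level of SAP 8.5, the 15% / 5% row gives 0.028 to 0.036, against 0.026 with no loss.

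*True rates 10% and 30%:*

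| Removed, MMF / Control | Difference (points) | Power |
|---|---|---|
| none | -20 | 0.832 |
| 10% / 10% | -19 to -18 | 0.807 to 0.779 |
| 15% / 5% | -20 | 0.844 to 0.856 |
| 5% / 15% | -18 to -16 | 0.764 to 0.682 |

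The sign of the error depends on which arm loses more, and on whether there is an effect.

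**The case against.** The strongest reply is SAP 8.5 itself. It distinguishes drop-outs from losses and stops collection only for losses. A withdrawal under 8.2 reads naturally as a drop-out, for whom data were collected. In 8.2, the only explicit stop to data collection is attached to consent withdrawal. Removal is also discretionary. The second sentence of 8.3 may be the working test, and protocol 7.5, 9.3.4 and 11.6 point to regular checks of medical records, questions about adverse events since the last visit, and medical records as source data.

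Much of this stands. Loss of data is a possibility, not a documented outcome. But the SAP sentence does not say whether collection went on after drop-out, nor whether it covers 8.2 withdrawals. If it does mean continued collection, it sits badly with a rule that takes the patient out of the study. The two definitions in 8.3 remain incompatible whichever was used.

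A reader might infer more than the documents support:

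- *That one missed procedure makes a patient lost.* 8.3 gives no count.
- *That 8.1 protects everyone whom 8.2 removes.* It covers the listed medical situations and severe flare, not behaviour or compliance.
- *That a patient who stops MMF must be removed.* No section says so.
- *That the loss falls mainly on the MMF arm and flatters MMF.* No figure is given by arm, and Control patients also buy their drugs (7.2.1) and can be withdrawn for compliance. One can assume that 5% to 15% of MMF patients leave at mid-follow-up with a 30% flare risk, and obtain 0.05 x 0.30 x 0.5 = 0.75 to 0.15 x 0.30 x 0.5 = 2.25 points of unseen flares. That sets Control loss to zero. At 10% removal in both arms, the same formula gives 1.5 points in each, and the contrast is unchanged.

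**Conclusion.** The point holds as an inconsistency that should be fixed. Taken as written, 8.2 and the first definition in 8.3 can end observation of patients who still consent and can be reached. 8.1 and the second definition would keep overlapping patients in, and SAP 8.5 does not settle the matter.

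The size is unknown. Equal removal gives no bias if there is no effect; at 10% per arm it costs about 2.5 to 5 points of power under the planned effect (0.832 to 0.807-0.779). An assumed 15% against 5% removal gives a spurious -1.5 to -3.0 points under no effect. These figures rest on assumed removal shares, on removed patients having their arm's flare rate, and on unseen flares counting as none. Uneven loss by arm is a credible risk, but its direction is not known. The conclusion that the four places must be reconciled does not depend on any of these numbers.

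**What to change.** Reconcile the four places in the direction that 8.1 already takes for follow-up:

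- **Protocol 8.2:** separate stopping the intervention from ending follow-up. An investigator's decision for safety, behaviour or compliance should not by itself end the scheduled assessments. Only withdrawal of consent or true loss of contact should.
- **Protocol 8.3:** delete the first definition and keep the second, which needs repeated missed visits together with failed contact.
- **SAP 8.5:** say that 8.2 cases stay under observation, and whether data on drop-outs are collected after the drop-out. State that a patient who misses a visit and returns is assessed for flares over the whole gap from existing medical records, which the Brief list already declares as a source.

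The cost is wording in three sections, plus scheduled visits kept for a few patients off treatment. The change concerns observation only and takes no position on when treatment should stop.

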## **8.3 Lost to follow-up**

The follow-up period of this research is 96 weeks, and every 24 weeks is a follow-up interval. When the research subject stops the scheduled follow-up, fails to complete the prescribed procedures of the research, or the investigator cannot contact the research subject regarded as lost to follow-up. A participant will be considered lost to follow-up if he/she repeatedly fails to return for scheduled visits and is unable to be contacted by the study site.

# **9. Evaluation of research outcomes**

## **9.1 Primary and secondary outcome evaluation**

The primary outcome was the proportion of patients who have flares (mild-to-moderate flares and severe flares) defined by modified SELENA-SLEDAI Flare Index (SFI) at 96 weeks of follow-up.

Secondary Endpoint:

- 1) The proportion of lupus low disease activity state (LLDAS) at week 96.
- 2) Short form-36 (SF-36) score of before and after treatment in two groups.
- 3) The proportion of adverse events of two groups in the follow-ups.
- 4) Changes in SLEDAI-2000 score.
- 5) Changes in prednisone dose.

## **9.2 Safety and other evaluations**

Safety indicators: clinical manifestations and signs of the patient, laboratory tests related to infection, laboratory tests related to SLE activity, such as complement, erythrocyte sedimentation rate (ESR), anti-dsDNA antibody titer and so on. Adverse events were reported regularly.

## **9.3 Adverse events and serious adverse events**

### **9.3.1 Adverse Event (AE) Definition**

According to ICH-GCP definition

An adverse medical event that occurs in a patient or clinical trial subjects following the use of a drug, but for which there is not necessarily a causal relationship between this medical event and treatment. Thus, an adverse event may be any adverse and unintended sign (including abnormal laboratory findings), symptom, or disease temporally associated with the use of a (study) drug,

regardless of whether it is related to the (study) drug. Currently, mycophenolate mofetil and glucocorticoids are used as first-line drugs in systemic lupus erythematosus. Infection could be considered as the most common AE of both glucocorticoids and immunosuppressants.

